### Statistical analysis

Data normality will be tested using the Kolmogorov-Smirnov or the Shapiro-Wilk *W* test. Parametric data will be presented as mean ± 95% CI. Non-parametric data will be log-transformed and presented as back-transformed mean ± 95% CI. The ES (Cohen’s *d*) will be calculated and interpreted as small (0.2–0.4), medium (0.5–0.7), or large (≥ 0.8).

Generalized linear mixed model analyses will be performed for each dependent variable, with group and time as fixed factors and patients as a random factor; the models will be adjusted by age, BMI, disease activity, and if different between groups, baseline values of the outcome variable. In the case of significant *F* values, a post-hoc test with Tukey’s adjustment for multiple comparisons will be performed. Analyses will be conducted according to the intention-to-treat principle, in which missing values will be handled by the generalized linear mixed model by using maximum likelihood to estimate the parameters of the model. To test the influence of reducing sedentary time on health-related outcomes, patients will be allocated into “responder” and “non-responder” sub-groups (according to changes in sedentary time); thereafter, the dependent variables will be compared between them.

Data analysis will be performed using the SAS 9.3 (SAS Institute Inc., Cary, NC, USA) for Windows. The level of significance will be set at *p* ≤ 0.050.

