Patients with rheumatoid arthritis spend 10.3 h/day on average in sedentary behavior [10, 18–21], which exceeds that in the general population (~ 7.5 h) [22], but is comparable to that in other clinical conditions (~ 9.4 h; pooled data for cardiovascular diseases [23], type 2 diabetes mellitus [24, 25]), and obesity [26, 27]). In these latter conditions, sedentary behavior is consistently related to morbidity and mortality [28–30]. Despite the paucity of evidence, it is plausible to assume that this might also hold true for patients with rheumatoid arthritis, since they commonly have cardiometabolic risk factors that can be aggravated by sedentary behavior [2–4]. To our knowledge, only a single study has addressed this topic, showing that an intervention involving general motivational counseling and text-message reminders resulted in reduced sedentary time (1.6 h/day), pain, and fatigue and improved quality of life in a Scandinavian cohort of patients with rheumatoid arthritis [31]. The cross-cultural validation of this finding in a Latin-American cohort with a lower socioeconomic status is necessary. In addition, exploring the putative mechanisms underlying the effects of reducing sedentary time requires novel studies. We aim to investigate the effects of a newly developed intervention focused on reducing sedentary time and its clinical, physiological, metabolic, and molecular effects in patients with rheumatoid arthritis.

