#### Physical activity level

Physical activity levels will be objectively measured using the actiGraph GT3X® accelerometers (ActiGraph, Pensacola, FL, USA). All patients will be instructed to wear the accelerometer during waking hours for 7 days consecutive, except when bathing or swimming. The device will be worn on a belt at the waistline on the right side of the hip. Data will be exported in 60-s epochs using ActiLife 6 software, v. 6.11.9 (ActiGraph, Pensacola, FL, USA). Patients will have to accumulate at least 10 h of valid activity recordings per day for at least 4 days, including one weekend day. Non-wear periods will be defined as intervals of at least 60 min of zero activity counts, assuming as tolerance no more than 2 min of counts between 0 and 100. Freedson cut-points will be used to define epochs: sedentary time (< 100 counts per minute (cpm)), light-intensity physical activity (≥ 100 to < 1952 cpm), and moderate-to-vigorous physical activity (≥ 1952 cpm) [36]. Actigraph GT3X® data will be reported as follows: time spent in sedentary behavior (hours/day), light-intensity physical activity (hours/day), moderate-to-vigorous physical activity (minutes/day), and moderate-to-vigorous physical activity accrued in ≥ 10-min bouts (minutes/day), total counts, and mean daily wear time. All data will be standardized to a 16-h day to avoid bias from differences in patients’ wear time, using the formula: (data × 16)/wear time.

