#### Clinical assessment

Disease activity will be assessed by the Disease Activity Score in 28 joints [37], which is based on the number of tender and swollen joints, C-reactive protein or erythrocyte sedimentation rate, and the patient’s general health status. Higher scores represent more severe disease activity. The Health Assessment Questionnaire [38], which evaluates physical functioning in eight domains of daily life, will also be used; higher scores represent greater disability. Disease duration, current dose of prednisone, current use of biological agents (e.g., anti-TNF, anti-IL6, anti-IL1, B cell depleting-agents, and T cell activation-inhibiters), non-biological disease-modifying anti-rheumatic drugs (e.g., methotrexate, leflunomide, and hydroxychloroquine), and other medications will be obtained by reviewing medical records and interviewing patients. Pain will be assessed using a visual analogic scale [39], in which patients grade their pain using a 10-point scale; 0 means no pain and 10 means severe or unbearable pain. Fatigue will be assessed by the Fatigue Severity Scale [40] in which lower scores indicate lower fatigue.

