#### Health-related quality of life

Health-related quality of life will be assessed by the SF-36 questionnaire [53], in which scales (physical function, role-physical, bodily pain, general health, vitality, social function, role-emotional) range from 0 to 100. Higher scores indicate better quality of life.

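### The blanket log-transformation rule cannot be carried out on secondary outcomes that include zero (pain, SF-36, bouted activity) and makes left-skewed bounded scores worse

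*Protocol article*

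**What the plan says.** The Statistical analysis section starts with a distributional check: "Data normality will be tested using the Kolmogorov-Smirnov or the Shapiro-Wilk" test. What fails has one destination: "Non-parametric data will be log-transformed and presented as back-transformed mean", with a 95% confidence interval. No exception, added constant or alternative is given. The section continues: "Generalized linear mixed model analyses will be performed for each dependent variable". On incomplete data it says that "missing values will be handled by the generalized linear mixed model by using maximum likelihood".

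Elsewhere the protocol describes outcomes that reach zero:

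- **Pain** (Clinical assessment): on the visual analogue scale "0 means no pain and 10 means severe or unbearable pain".
- **SF-36** (Health-related quality of life): the scales "range from 0 to 100", higher being better.
- **Bouted activity** (Physical activity level): minutes per day of moderate-to-vigorous activity in bouts of at least 10 minutes. A patient with no such bout scores 0.

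For the primary outcome, the Introduction says: "Patients with rheumatoid arthritis spend 10.3 h/day on average in sedentary behavior".

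**The concern.** A rule that sends every non-normal outcome to the log scale has no meaning at zero. The outcomes concerned are not marginal to the trial's aims: the second main hypothesis is about clinical parameters, cardiometabolic risk and quality of life, so pain and SF-36 are direct tests of it.

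Whoever runs the analysis will meet a zero and have to improvise. Each obvious improvisation has a cost:

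- If the logged zero becomes a missing value, it is missing because of what it was. Maximum likelihood treats it as ignorable.
- If a constant is added first, the estimate depends on a number chosen at that moment, possibly with the data in view.

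The log also pulls in only the right tail. A bounded score that fails normality because it bunches near its upper limit becomes more skewed, and the plan offers no other route for it.

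**Working it through.** The plan states no figure for this point, so there is none to reproduce. The document gives no distribution for these outcomes. All shapes and zero shares below are assumptions.

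**1. How likely is a zero?** The minimum planned sample is 30. If a share p scores zero at a visit, the chance of at least one zero is 1 − (1 − p)^30.

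| p | Expected zeros (30p) | Chance of at least one |
|---|---|---|
| 5% | 1.5 | 1 − 0.95^30 = 0.785 |
| 10% | 3 | 1 − 0.90^30 = 0.958 |
| 20% | 6 | 1 − 0.80^30 = 0.999 |

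**2. Would the rule be triggered?** Simulated Shapiro-Wilk tests at p ≤ 0.05, 30 values at one visit:

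- Pain, normal with mean 4 and SD 2.5, rounded and limited to 0–10, both arms together: normality is rejected in about 19%, 33% and 61% of samples for intervention shifts of 0, -1 and -2. Pooling both visits (60 values treated as independent) gives about 79% and 91% for -1 and -2.
- Bouted activity with 10%, 20% or 40% zeros and lognormal positive values (log SD 0.8): rejection together with at least one zero occurs in about 88%, 96% and over 99%. With log SD 0.5 the figures are about 40%, 63% and 98%.

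The trigger is plausible for pain and likely for bouted activity. It depends on the unit tested, which the article does not state.

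**3. If zeros are dropped: the simplest case.** Let the zero shares be p0 (control) and p1 (intervention), with identical non-zero scores.

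- Raw mean ratio = (1 − p1)/(1 − p0).
- Log ratio among non-zeros = 1.00, whatever p0 and p1 are.

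At 10% vs 10% both ratios are 1.00, so there is no between-arm bias. At 10% vs 30% the raw ratio is 0.70/0.90 = 0.78 and the log ratio is still 1.00, so the effect is missed.

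**4. If zeros are dropped: a shift in pain.** Same pain distribution as in step 2. The zero share is Φ((0.5 − mean)/2.5); the means follow from the probabilities of the scores 0 to 10.

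| Arm | Zero share | Mean | Geometric mean of non-zeros |
|---|---|---|---|
| Control | Φ(−1.4) = 8.1% | 4.05 | 3.81 |
| Shift -1 | Φ(−1.0) = 15.9% | 3.14 | 3.16 |
| Shift -2 | Φ(−0.6) = 27.4% | 2.30 | 2.66 |

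- Shift -1: raw ratio 3.135/4.050 = 0.774; log ratio 3.16/3.81 = 0.83.
- Shift -2: raw ratio 2.295/4.050 = 0.567; log ratio 2.66/3.81 = 0.70.

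A ratio of arithmetic means and a ratio of geometric means are different quantities, so the gap shows direction rather than a pure bias. Step 3 isolates the effect of dropping zeros.

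**5. If a constant c is added.** With p0 = 10%, p1 = 30% and equal non-zero scores, the back-transformed ratio is exp{(p1 − p0) × [ln c − mean of ln(X + c) among non-zeros]}. With non-zero scores lognormal (median 3.5, log SD 0.5), rounded and limited to 1–10:

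| c | Ratio |
|---|---|
| 0.01 | 0.31 |
| 0.1 | 0.49 |
| 0.5 | 0.66 |
| 1 | 0.74 |

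The raw mean ratio is 0.78 throughout. The constant decides the answer.

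**6. Left skew.** For an illustrative 0–100 score bunched near its ceiling (100 × beta(4, 1.2)), skewness goes from -0.88 to -1.83 on taking logs.

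**The case against.** The best defence is that the article never says zeros will be dropped. An analyst has to do something at zero, and a condensed article commonly leaves that detail to an analysis plan. The models are described as generalized, so non-normal distributions are available. This stands as far as the harm is concerned: loss of data is one possible consequence, not a stated procedure. It does not save the rule, because the article commits to a single transformation that cannot be carried out on outcomes it defines. That is a choice fixed badly, not a detail left out.

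Some stronger readings are tempting but unsupported:

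- **Patients would be lost.** A zero at one visit would remove that visit's value; the mixed model keeps the patient's other visits.
- **The best responders would be lost.** A zero pain score at baseline is not a response, and zeros in bouted activity belong to the least active patients.
- **Intention-to-treat is broken.** Patients would still be analysed as randomised. The problem would be informative missingness of some values.
- **Effects would be biased.** Between-arm bias arises mainly when zero shares differ by arm, after the normality test has failed and zeros have been dropped.
- **Normality is tested on raw variables rather than residuals.** The article speaks only of data normality, so this is an inference.
- **HAQ is affected too.** The article gives no range for it.

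**Conclusion.** The point holds as a defect in a stated rule for secondary outcomes. The log transformation cannot be applied to zero scores on pain or SF-36, or to zero minutes of bouted activity, and it worsens left-skewed bounded scores. No way of meeting the zeros is neutral: dropping them can hide or shrink an effect when zero shares differ by arm, and adding a constant moves the ratio from 0.31 to 0.74 in the example.

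The primary outcome is not touched, since sedentary time of about 10 h/day is far from zero. Strictly positive laboratory markers are not touched by the zero problem either. The size of any bias in this trial is unknown. The 0.83 against 0.77 and 0.70 against 0.57 comparisons rest on an assumed pain distribution and leave out baseline values, the mixed model and the normality-test trigger. They should not be read as forecasts. The change is worth making before analysis because it is cheap and bears on outcomes named in the second hypothesis.

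**What to change.** Replace the blanket rule in the Statistical analysis section with wording to this effect:

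- Log transformation is limited to strictly positive, right-skewed variables such as laboratory markers.
- Model fit is judged on residuals, not by a normality test that automatically selects the scale.
- Bounded or zero-containing outcomes (pain, SF-36 scales, bouted activity, and any other outcome found to include zeros) are analysed untransformed with robust or bootstrap intervals, or with a generalized mixed-model distribution that admits zeros.
- The choice for each outcome is fixed before the data are unblinded. If a constant is ever added before taking logs, its value is fixed then too.

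The cost is a few lines of text and slightly more programming. No change to design, sample size or data collection is needed.

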Cardiac and sympathetic spontaneous baroreflex sensitivity will be assessed from the fluctuations of the RR interval, blood pressure, and muscle sympathetic nerve activity, using CardioSeries (v. 2.4, São Paulo, Brasil) software. Cardiac baroreflex sensitivity will be assessed using the sequence technique [49]. Sympathetic baroreflex sensitivity will be assessed from the linear regression analysis between the area of sympathetic bursts and the corresponding diastolic blood pressure. The slope of the linear regression line will be used as an index of sympathetic baroreflex sensitivity [50].

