#### Lipidomics (non-targeted)

PRE and POST intervention serum samples (10 μL) will be collected from a random sub-sample of 20 patients (Fig. 5). Samples will be extracted in a single-phase extraction with 200 μL of CHCl3:MeOH (2:1) and 10 μL of an internal standard mix containing between 50 and 1000 pmol each of 23 non-physiological and stable isotope-labeled lipid standards. Sample analysis will be performed by electrospray ionization tandem mass spectrometry with the use of an Agilent 1200 liquid chromatography system combined with an Applied Biosystems API 4000 Q-TRAP mass spectrometer with a turbo-ion spray source (350 °C) and Analyst 1.5 data system. Solvent composition will comprise tetrahydrofuran-methanol-water with 10 mM ammonium format, at the following ratios; solvent A 20:20:60 and solvent B 75:20:5. All lipid species will be separated under gradient conditions at 300 μL/min, the gradient starting at 0% solvent B to 45% solvent B over the first minute, to 55% solvent B over 6 min, up to 80% solvent B over 1 min, up to 100% solvent B over 2 min, holding at 100% solvent B for 2 min, quickly back to 0% solvent B over 0.2 min and then holding at 0% solvent B until the next injection at 15.5 min. A total of 338 lipid species will be analyzed by multiple reaction monitoring experiments. This type of lipidomic measure is semi-quantitative, because stable isotope internal standards are not available for each individual lipid species. However, the precision of such measures is considered good (average coefficient of variation (CV) typically < 10%). We will report fasting lipid concentrations to provide an indication of the relative abundance of each lipid species or class. Lipid concentrations reported for lipid classes and subclasses will be calculated from the sum of the individual lipid species within each class. Finally, the percentage change in lipid species (PRE to POST) will be compared between groups (control and intervention groups).

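### The only stated remedy for non-normal outcomes is a log transformation, which is undefined for several listed secondary outcomes that can be zero or negative

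*Protocol article*

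**What the plan says.** The Statistical analysis section starts with a normality check: "Data normality will be tested using the Kolmogorov-Smirnov or the Shapiro-Wilk" test. Outcomes that fail it, which the article calls non-parametric, have one route: "Non-parametric data will be log-transformed", with the back-transformed mean and its confidence interval reported. No offset, exempted outcome or other method is named. The model then applies to everything: "Generalized linear mixed model analyses will be performed for each dependent variable". The analysis is declared intention-to-treat, and missing values are left to the likelihood fit of that model.

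Other sections define outcomes whose range includes zero:
- Pain (Clinical assessment): "0 means no pain and 10 means severe or unbearable pain".
- SF-36 scales (Health-related quality of life): these "range from 0 to 100".
- Moderate-to-vigorous activity in bouts of at least 10 min (Physical activity level): zero if no bout occurs.
- Blood pressure load (Blood pressure): a percentage of readings above a threshold, so zero if none is.

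Others can be negative:
- Nocturnal blood pressure fall (Blood pressure): day minus night over day, negative if night exceeds day.
- Sympathetic baroreflex sensitivity (Cardiovascular autonomic function): "The slope of the linear regression line will be used as an index of sympathetic baroreflex sensitivity", and a slope can take either sign.
- Lipids (Lipidomics): "the percentage change in lipid species (PRE to POST) will be compared between groups", negative whenever a species falls.

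**The concern.** This is a stated rule that cannot be carried out on outcomes the same article defines. It is not a detail merely left unsaid. If an analyst follows it as written, the log of a zero or negative value is returned as missing, and the mixed model then treats it like any other missing value.

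Likelihood estimation is valid if the chance of being missing does not depend on the unseen value, given what is observed. Here the unseen value determines it completely. For pain, the records lost are the best results, so an effective intervention loses its own successes. For SF-36 the records lost are the worst scores. SF-36 scales bunched near 100 would also become more left-skewed on the log scale, so the remedy would not do its job there either.

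What is at stake is the second main hypothesis, on clinical parameters, cardiometabolic risk factors and quality of life.

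**Working it through.** The article gives no figure to reproduce here. The claim rests on the domain of the logarithm and on the ranges listed above: log(0) is minus infinity and log(-5) is undefined.

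**Inputs.** From the article: 30 patients (taken as 15 per arm) and a pain scale starting at 0. Everything else is assumed: pain approximately normal, rounded to whole points, values below 0 recorded as 0, SD 2.5, PRE-POST correlation 0.6, control mean 4 (or 3), true shift of -2 points at POST.

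**Step 1: POST records without a log.** A score is recorded as 0 if the underlying value is below 0.5, so the share is Φ((0.5 − mean)/2.5).

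| Control mean | Intervention POST | Control POST |
|---|---|---|
| 4 | Φ((0.5−2)/2.5) = Φ(−0.6) = 27% | Φ((0.5−4)/2.5) = Φ(−1.4) = 8% |
| 3 | Φ((0.5−1)/2.5) = Φ(−0.2) = 42% | Φ((0.5−3)/2.5) = Φ(−1.0) = 16% |

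**Step 2: whole patients lost.** The mixed model keeps a patient who has one usable visit. By simulation, zeros at both visits occur in 6% v 3% (intervention v control) at mean 4 and in 13% v 7% at mean 3. A zero at either visit is more common, 30% v 13% at mean 4, but that would count as loss only if whole pairs were deleted.

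**Step 3: effect on the estimate.** Removing zeros divides each arm's mean by its non-zero share, so the ratio of means R becomes R × (1 − control zero share)/(1 − intervention zero share).
- Mean 4: R = 0.57 with everyone. Without zeros, 0.57 × 0.92/0.73 = 0.72. The simulated log-scale ratio among non-zero POST values is 0.70.
- Mean 3: R = 0.50 with everyone. Without zeros, 0.50 × 0.84/0.58 = 0.72. The simulated log-scale ratio is also 0.72.

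The arithmetic and log-scale ratios agree closely, so the dilution comes from losing the zeros and not from the change of scale. Restricting to non-zero pairs, with or without baseline adjustment, gives 0.66 to 0.69 at mean 4.

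**Step 4: a different assumption.** Suppose the intervention only raises the zero share from 10% to 30% and leaves positive scores alone. Then R = 0.70/0.90 = 0.78, a simulated difference of -0.89 points. Without zeros the ratio is 0.78 × 0.90/0.70 = 1.00, so the effect disappears. Keeping everyone with log(x+1) gives 0.73.

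**Step 5: does the rule fire?** With equal zero shares of 5%, 10% and 20% in both arms, about 1.5, 3.0 and 6.0 of 30 values per visit have no log, and Shapiro-Wilk rejects in 39%, 38% and 68% of runs. At 20% v 40%, 9.0 of 30 values have no log and it rejects in 93%. In the mean-4 scenario it rejects in about 16% of runs on PRE values, 62% on POST values and 6% on model residuals. The article does not say which of these is tested.

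**The case against.** **The article does not say that zeros are discarded.** It declares intention-to-treat, and an analyst could add a constant. This stands as far as it goes: the loss follows from literal application and is not a stated exclusion. But no constant is given, and its choice changes a back-transformed effect, so it should not be made after the data are seen.

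**The scale of each outcome is SAP detail that an article may omit.** This would settle the matter if the article were silent. It is not silent. It fixes one rule for all non-normal data, and that rule fails on its own outcomes. The generalized linear mixed model could accommodate other distributions and links, but the article names none and sends non-normal data to the log instead.

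**The size is conditional.** This stands. The rule applies only if normality fails. The pain distribution is assumed: had it been truncated at zero, with no pile-up at 0, zeros at either visit would fall to 9% v 4-5% at mean 4. A reader might also quote a fall in power from 69% to 42% at mean 4. That figure supposes that the log is always used and that whole PRE-POST pairs are deleted under ANCOVA, which is not the planned model. With log(x+1) and all patients kept, power is about 66%, so the harm lies in losing records and not in the log as such.

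**Lipids.** A reader might infer that about half of the 20 sub-sample patients would be lost, since about half of the changes are negative when nothing changes. The Lipidomics section does not say that percentage change is logged. The loss would arise only if percentage change failed the normality test and was then logged directly.

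**Conclusion.** The point holds for secondary and mechanistic outcomes. The only stated remedy for non-normality cannot be carried out on outcomes that can be zero or negative. If followed literally, it removes visit records according to their own value and can dilute a real effect. Under the assumed pain scores with mean 4, about 27% v 8% of POST records go and a ratio of 0.57 appears as about 0.70. Under the assumption that only the zero share changes, the effect vanishes. The true size is unknown, because the article gives no zero shares and no pain distribution.

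Three stronger readings are not supported:
- The primary outcome is not threatened; sitting time in hours per day is positive.
- Patients are not generally dropped from their own analysis. A whole patient is lost only if both visits are zero or if the outcome is a single change value.
- The article does not openly contradict its intention-to-treat statement. The conflict arises only if the rule is applied as written.

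Several affected measures (ambulatory blood pressure, autonomic function, lipidomics) are also taken only in random sub-samples. The rule should be corrected before analysis, but it does not endanger the trial's main result.

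**What to change.** Replace the blanket rule with a short table that gives the analysis scale of each outcome:
- Log only for strictly positive, right-skewed variables, such as C-reactive protein, cytokines, insulin and triglycerides.
- For outcomes that contain zeros, are bounded or can change sign, use the original scale, or a suitable distribution and link in the mixed model already planned. A prespecified offset (for outcomes that reach zero but are not negative) or a rank-based method is also acceptable. Any of these will do if it is named in advance and keeps all randomised patients.
- Analyse lipid species as log concentration at PRE and POST. The back-transformed contrast is still a relative change, and no signed percentage has to be logged.

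The cost is the table itself. The downside is that some outcomes will be reported as differences instead of ratios.

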### Experimental design

We will conduct a 4-month, parallel-group, randomized controlled trial, in which patients will be assessed at baseline (PRE) and after 4 months (POST) for sedentary behavior (primary outcome) and physical activity levels; clinical parameters; anthropometric parameters and body composition; aerobic fitness; muscle function; blood pressure; cardiovascular autonomic function; vascular function and structure; health-related quality of life; blood samples and oral glucose tolerance test; immune function; muscle biopsy; and food intake. Sedentary behavior and physical activity levels will be also evaluated at the second month to check adherence to the intervention.

After baseline assessments, patients will be randomly allocated to either a control or intervention group using a simple randomization (1:1 ratio) procedure, by computer-generated random numbers in SAS 9.3 (SAS Institute Inc., Cary, NC, USA) for Windows. An external researcher will generate the allocation sequence and be contacted after patients’ enrollment. All assessors will be blinded to patients’ allocation and will be responsible for patients’ recruitment and enrollment. However, a trained researcher who will not be blinded to patients’ allocation will be responsible for assigning patients, and for applying and monitoring the Take a STAND for Health intervention. The control group will receive standard care, including general advice on healthy lifestyle. The intervention group will receive standard care supplemented with a specific personalized intervention aimed at reducing sedentary time (called Take a STAND for Health), which will not require alteration to usual care pathways (including use of any medication). In brief, this intervention comprises individually tailored progressive goals aimed at reducing sedentary time, which will be selected with the active participation of the patient. A trained researcher will assess adherence to the goals via phone calls and personal interviews throughout the follow up.

The current study is registered in an international database of clinical research studies (clinicaltrials.gov, NCT03186924). This manuscript is described according to the Standard Protocol Items: Recommendations for Interventional Trials (SPIRIT) checklist (Fig. 1, Additional file 1) and the findings from this study will be reported according to the recommendations of the Consolidated Standards of Reporting Trials (CONSORT) guidelines (Fig. 2).

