#### Sample size

Sample size calculations were performed using G-Power® software, v. 3.1 (Universität Düsseldorf, Düsseldorf, Germany), based on the study by Lewis et al. that reported the effects of reducing sedentary behavior in an elderly population (i.e., a reduction of 52 min in total sitting time) [33]. According to the estimation, 24 patients (12 per arm) are required to achieve 95% power (α), with a significance level of 5% (β), and assuming an effect size of 0.58 for the primary outcome (i.e., sedentary time). Estimating a dropout rate of ~ 25%, at least 30 patients will be recruited. Considering that this sample size could be underpowered for some secondary outcomes, we will try to increase this estimated sample based on the feasibilities of our laboratory (including funding, capacity of research staff and facilities, and available patients), in line with contemporary recommendations [34, 35].

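### The outcome's baseline value is adjusted for only if the groups happen to differ, and on the natural reading of the model that adjustment would leave the treatment contrast almost unchanged

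*Protocol article*

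**What the plan says.** The Statistical analysis section prescribes a generalized linear mixed model for each dependent variable, "with group and time as fixed factors and patients as a random factor". On covariates it says that "the models will be adjusted by age, BMI, disease activity, and if different between groups, baseline values of the outcome variable". It gives no criterion for deciding that groups differ, and no other section makes baseline adjustment unconditional.

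The Experimental design section says "patients will be assessed at baseline (PRE) and after 4 months (POST", so the baseline visit is one of the levels of time. For the primary outcome there is one further measurement: "Sedentary behavior and physical activity levels will be also evaluated at the second month to check adherence to the intervention". Allocation is made "using a simple randomization (1:1 ratio) procedure", with no stratification mentioned. The Sample size section requires 24 patients (12 per arm), "assuming an effect size of 0.58 for the primary outcome", and plans to recruit at least 30 to cover about 25% dropout.

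**The concern.** In a randomized trial a baseline difference between arms is chance, so its observed size is a poor reason for choosing a covariate. A covariate should be chosen because it predicts the outcome, and the outcome's own baseline value usually predicts it well. A rule that looks at the data first makes the model unknown until the data are in. It also leaves moderate imbalances untouched, and these are common with 12 to 15 per arm under simple randomization.

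There is a second, less visible problem. If the baseline measurement is already one of the responses, adding it again as a covariate main effect does not act on the comparison of interest. The adjustment that the section promises may then do next to nothing, whether or not the condition is met. Precision in a very small trial is at stake, as is the extent to which one unlucky allocation colours the reported effect.

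**Working it through.** The protocol gives no figure for this rule, so there is none to reproduce. The check uses these inputs:

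- From the protocol: 12 per arm (analysed) or 15 per arm (recruited), and effect size 0.58. The type of effect size is not stated; it is taken here as a between-group difference in units of the outcome's SD at one visit.
- Assumed: PRE-POST correlation rho of 0.5, 0.7 or 0.8 (not given), equal SD at both visits, a two-sided 5% test, and p ≤ 0.05 as the meaning of a baseline difference.

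**1. What the rule leaves unadjusted.** The largest gap that is not significant is t × sqrt(2/n) in SD units.

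- 12 per arm: 2.074 × sqrt(2/12) = 0.85 SD.
- 15 per arm: 2.048 × sqrt(2/15) = 0.75 SD.

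The standard error of the baseline difference is sqrt(2/12) = 0.41 SD or sqrt(2/15) = 0.37 SD. A gap beyond 0.5 SD in either direction thus arises in about 22% or 17% of trials, while the trigger fires in only about 5%.

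**2. What the covariates do to the contrast.** With PRE and POST as responses and complete data, the group-by-time estimate is (POST − PRE, intervention) − (POST − PRE, control). A covariate that is constant within a patient and enters as a main effect cancels in POST − PRE. Random-intercept models fitted to four complete simulated data sets (12 per arm) confirmed this. The estimate was identical to four decimals without covariates, with age, BMI and disease activity, and with the outcome's baseline added (for example −1.1294 each time; ANCOVA on the same data gave −1.0392). With 6 of 24 POST values missing, the three covariates moved it by 0.004 to 0.09 SD.

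**3. How imbalance enters.** Given a baseline gap D and true effect τ, the expected POST difference is τ + rho × D. The expected difference in change is therefore τ + rho × D − D = τ − (1 − rho) × D. Simulated slopes on D were −0.51, −0.30 and −0.20 at rho 0.5, 0.7 and 0.8; for ANCOVA they were about 0.

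A gap of 0.5 SD shifts the estimate by 0.25, 0.15 or 0.10 SD. The SD in minutes is not stated. Dividing the cited 52-minute reduction by 0.58 gives about 90 minutes, and the shift is then about 22, 13 or 9 min/day. With the pilot's baseline SD of 1.3 h (78 minutes) it is about 20, 12 or 8 min/day.

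**4. Precision.** The large-sample variance is proportional to 2(1 − rho) for change and 1 − rho² for ANCOVA, a ratio of 2/(1 + rho). The simulated columns are for 12 per arm and a true difference of 0.58 SD; power figures are good to about one point.

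| rho | Variance ratio, change/ANCOVA | SD of estimate, change vs ANCOVA | Power, change vs ANCOVA |
|---|---|---|---|
| 0.5 | 2/1.5 = 1.33 | 0.41 vs 0.37 | 28% vs 34% |
| 0.7 | 2/1.7 = 1.18 | 0.32 vs 0.30 | 41% vs 46% |
| 0.8 | 2/1.8 = 1.11 | 0.26 vs 0.25 | 57% vs 59% |

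At 12 per arm the simulated variance ratios are a little smaller (1.29, 1.13, 1.05), because ANCOVA must estimate a slope.

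**5. Does the condition rescue the analysis?** Suppose, generously, that a triggered trial switched to full ANCOVA. At rho 0.5 the variance would be 0.159, against 0.169 for change and 0.131 for ANCOVA, so most of the loss would remain.

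**The case against.** The strongest reply is that nothing here is invalid. The change contrast is unbiased over randomizations. A simulation of the conditional rule with a 5% trigger and a switch to ANCOVA when it fires (20,000 trials, 12 per arm) gave type I error of 4.6%, 4.4% and 4.7% at rho 0.5, 0.7 and 0.8. The power loss is a few points and is small at rho 0.8; the true correlation is not in the document. This stands, and it limits the point to lost precision and to bias conditional on the observed imbalance.

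The model is also partly inferred. The group-by-time term is not named, and the section does not say how the baseline covariate would enter. If baseline were a covariate for follow-up values only, adjustment would work. The month-2 measurement makes that reading possible for the primary outcome, although that visit is described as an adherence check. For outcomes measured only at PRE and POST, keeping PRE as a response is the natural reading.

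Three stronger inferences are tempting, and the document does not support them:

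- **That the covariates can never change the effect.** This is exact only for time-constant main effects with complete data, and the trial expects about 25% dropout.
- **That baseline information is thrown away.** With PRE among the responses it is used, though less efficiently than in ANCOVA.
- **That BMI and disease activity will enter as post-randomization, time-varying covariates.** The Clinical assessment section says only that "Disease activity will be assessed by the Disease Activity Score in 28 joints". No section says that follow-up values will serve as covariates.

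**Conclusion.** The point holds as a matter of efficiency and pre-specification, and the plan should be changed. The conditional clause ties the model to chance imbalance by an unstated criterion. On the natural reading, the adjustment would leave the estimate essentially a difference in change, carrying −(1 − rho) times the baseline gap. Compared with ANCOVA, the variance is about 11% to 33% higher in large samples, and 2 to 6 points of power are lost at 12 per arm.

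These sizes rest on the assumed correlations of 0.5 to 0.8, a 5% trigger, equal SDs at the two visits and 0.58 read as a standardized between-group difference. A reader might infer that the primary result will be biased or its error rate inflated; the checks do not show that. How the sample size of 24 was obtained is a separate question, and this point does not depend on it.

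**What to change.** - Delete the clause that makes baseline adjustment conditional, and do not choose covariates from observed baseline differences.
- For every outcome, model the follow-up value or values with group (by visit where there is more than one) and always include the outcome's own baseline value (ANCOVA, or a mixed model for repeated measures). Alternatively, use a constrained longitudinal model in which both arms share one baseline mean.
- State that age, BMI and disease activity enter as baseline values.

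The first change is not enough by itself: while PRE stays among the responses, baseline as an unconditional main effect still leaves the contrast unchanged.

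The cost is wording and one degree of freedom for the baseline slope. PRE values are already planned for every patient, so no visit or measurement is added. The Trial status section still expected recruitment to end in February 2020 and follow-up in June 2020. The document therefore does not show that data collection was complete, and the change is best recorded before the data are analysed.
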